### Blind success rate evaluation

2.9

A blinded assessment will be conducted 5–10 min after the final treatment session in the 4 weeks for both the acupuncture and sham acupuncture groups. Patients will complete a questionnaire indicating whether they believed they received acupuncture, with response options of “Yes,” “No,” or “Uncertain.” The number of responses in each category will be recorded separately. Then, the Bang’s Blinding Index (BBI) will be used to calculate for each group according to Bang’s index formula (27). BBI values ranged from −1 to 1, with results closer to −1 indicating more successful blinding. A BBI value of < 0.2 was considered indicative of successful blinding. In addition, the recruitment rate and compliance of the patients will be statistically analyzed.

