**Figure 1 fig1:**
[figure not shown]
Study flowchart. MAS, Modified Ashworth Scale; CSI, Clinical Spasticity Index; NIHSS, National Institutes of Health Stroke Scale; FMA, Fugl-Meyer Motor Assessment; MBI, Modified Barthel Index; sEMG, Surface Electromyography; SWUE, Shear-wave ultrasound elastography.

**Table 1 tab1:** Schedule of enrollment, interventions, and assessments.

Time points	Enrollment	Baseline	Treatment period				Follow-up period	
	Week 1	Week 0	Week 1	Week 2	Week 3	Week 4	Week 6	Week 8
Screening and recruitment								
Inclusion and exclusion	x							
Clinical interview	x							
Sign the informed consent	x							
Randomization		x						
Interventions								
Acupuncture group			12 sessions of treatment (3 times a week)					
Sham acupuncture group			12 sessions of treatment (3 times a week)					
Basic treatment group			No acupuncture treatment					
Assessments								
MAS		x		x		x	x	x
FMA		x		x		x	x	x
CSI		x		x		x	x	x
NIHSS		x		x		x	x	x
MBI		x		x		x	x	x
sEMG		x				x		
SWUE		x				x		
Others								
Adverse events			x	x	x	x		
Blinding assessment			x	x	x	x		
Patients’ compliance			x	x	x	x		
Type of stroke		x						
Patients’ complications		x						

MAS, Modified Ashworth scale; FMA, Fugl-Meyer motor function assessment; CSI, comprehensive spasticity scale; NIHSS, National Institutes of Health Stroke Scale; MBI, Modified Barthel Index; sEMG, surface electromyography; SWUE, Shear-wave ultrasound elastography.

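### Section 2.9 treats −1 as the best value of Bang's blinding index, but the no-information value is 0, and its per-group rule of below 0.2 can misjudge blinding in both directions

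*Protocol article*

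**What the plan says.** Section 2.9 of the protocol article (Blind success rate evaluation) plans a blinding check "for both the acupuncture and sham acupuncture groups", 5–10 minutes after the last session of the 4-week course. "Patients will complete a questionnaire indicating whether they believed they received acupuncture"; they may answer Yes, No or Uncertain, and the count in each category is recorded.

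On the calculation: "the Bang’s Blinding Index (BBI) will be used to calculate for each group according to Bang’s index formula". On interpretation, the range is given as −1 to 1, "with results closer to −1 indicating more successful blinding". On the decision: "A BBI value of < 0.2 was considered indicative of successful blinding". No lower limit is given, and no other section of the article corrects the direction or changes the rule.

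Table 1 has a row "Blinding assessment" marked in each of weeks 1, 2, 3 and 4, whereas section 2.9 describes a single assessment after the final session.

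**The concern.** Blinding is adequate when a patient's answer says little about the group to which the patient was assigned. On an index that runs from −1 to 1, both ends describe answers tied completely to allocation, so neither end can be the ideal. The article names one of them as the ideal and then sets a pass rule that is open at that end.

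The sham arm exists to separate needling effects from expectation. The Introduction says placebo effects are incompletely characterised, the Discussion faults earlier trials for inadequate blinding, and section 3.1 relies on the blunt retractable needle to keep participants blinded. Section 2.9 is the article's only stated test of whether that worked. A wrong criterion could lead the report to claim successful blinding where belief differed between groups, or to concede failure where belief was the same.

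**Working it through.** **Inputs.** From section 2.9: three answer categories, one index per group, range −1 to 1, success if below 0.2. From section 2.11: 48 evaluable and 60 randomised patients per group. The answer percentages below are assumptions for illustration.

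**Formula.** The article names Bang's index without printing it. Per group,

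B = (correct − incorrect) / (correct + incorrect + uncertain).

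Yes is correct under acupuncture; No is correct under sham.

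**Anchor points, n = 60**
- All correct: (60 − 0)/60 = +1
- All wrong: (0 − 60)/60 = −1
- Random guessing, 30 right and 30 wrong: 0/60 = 0
- Random guessing, 20 right, 20 wrong, 20 uncertain: 0/60 = 0

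This reproduces the article's range and puts the no-information value at 0. For both groups to reach −1, every acupuncture patient must say No and every sham patient Yes. Reversing the sign would not rescue the text, because −1 would then mean that everyone guessed correctly.

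**Both groups together.** B(acupuncture) = Yes − No in that group; B(sham) = No − Yes in that group. If the answers have the same distribution in both groups, the two values are equal and opposite and sum to 0. Both therefore cannot approach −1 when belief is unrelated to allocation.

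**False pass (from the missing lower bound)**
- Acupuncture, 20% Yes / 60% No / 20% Uncertain: 0.20 − 0.60 = −0.4, pass
- Sham, 60% Yes / 20% No / 20% Uncertain: 0.20 − 0.60 = −0.4, pass
- Difference in Yes: 20% − 60% = −40 points. Standard error at 60 per group: √[(0.2×0.8 + 0.6×0.4)/60] = 0.082, 95% interval about −56 to −24 points

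**False fail (from reading each group alone)**
- Both groups 60% Yes / 20% No / 20% Uncertain
- Acupuncture: 0.60 − 0.20 = +0.4, fail
- Sham: 0.20 − 0.60 = −0.4, pass
- Sum 0; difference in Yes 0 points

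**Precision.** SE(B) = √{[p₁ + p₂ − (p₁ − p₂)²]/n}, where p₁ and p₂ are the proportions correct and incorrect. For 60/20/20: √[(0.8 − 0.16)/60] = 0.103, half-width 0.20; with n = 48, 0.115 and 0.23. For 40/40/20: √(0.8/60) = 0.115, half-width 0.23; with n = 48, 0.129 and 0.25.

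**Chance behaviour of the stated rule (exact calculation)**

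| True index | n = 60 | n = 48 |
|---|---|---|
| 0, no Uncertain: one group fails | 7.8% | 9.7% |
| 0, no Uncertain: at least one of two groups fails | 14.9% | 18.4% |
| 0, one third Uncertain: one group fails | 3.4% | 4.6% |
| 0.3: group passes | 16–17% | 20–21% |

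**Would a band of −0.2 to 0.2 per group be enough?** It stops the false pass. In the identical-belief case it fails both groups (+0.4 and −0.4), and at a true index of 0 with no Uncertain answers it raises chance failure per group to 15.5% (n = 60) or 19.3% (n = 48).

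**The case against.** The strongest defence is that little depends on this check. Section 2.12 does not use it in any efficacy analysis, and answers are recorded by category, so a sound index and comparison can be computed later from the planned data. This stands, and it limits the seriousness of the point.

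The false-pass example is also unlikely. Section 2.6 has real needling seek deqi while the sham gives only a pricking sensation, so the likelier failure is sham patients recognising the sham. That gives a positive sham index, which the rule would flag. A negative index in the sham group alone, where patients believe the needling was real, is often acceptable. This too stands, but section 2.9 applies the rule to each group, and its statement about −1 is wrong whichever pattern occurs. The false fail needs only that most patients in both groups believe they had real needling.

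Three stronger readings are tempting and are not supported:
- *The missing lower bound causes both errors.* It causes only the false passes. The false fails come from reading each group alone, and from chance around a point estimate.
- *A 0.2 cut-off cannot decide anything at this sample size.* The chance figures show an imprecise rule that still discriminates.
- *The question is defective because it asks about acupuncture rather than real versus sham.* The article only paraphrases the questionnaire, and neither the form nor the consent wording is shown.

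The absence of intervals from an article is not itself a fault, since a full protocol or analysis plan may hold them. They enter here only as part of replacing a rule that is stated wrongly.

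**Conclusion.** The point holds as a wrong statement and a wrong rule in section 2.9. The best value of the index is 0, not −1. As written, the rule can pass both groups at −0.4 with a 40-point difference in belief, and can fail acupuncture at +0.4 with no difference in belief. The direction error follows from the definition of the index and needs no assumption; the two examples rest on assumed answer patterns.

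A reader might infer that the trial's efficacy result is compromised. It is not: the primary MAS analysis does not use the index. The effect is confined to how blinding, and hence the sham comparison, is interpreted. The point deserves correction but does not threaten the trial's main analysis. The timing mismatch with Table 1 is a separate, minor inconsistency.

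**What to change.** In section 2.9:
1. Delete the statement that values nearer −1 mean better blinding. State that 0 is random guessing, +1 is all correct and −1 is all wrong.
2. Replace the one-sided per-group rule with the index and its 95% confidence interval in each group, read jointly: acupuncture positive with sham about equally negative indicates similar belief.
3. Report the between-group difference in the proportion answering Yes, with its confidence interval.
4. Do not substitute ±0.2 as a stand-alone pass/fail limit per group.
5. As a minor point, reconcile Table 1 (weeks 1 to 4) with section 2.9 (once, after the final session).

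Items 1 to 4 cost a text change and a simple analysis of answers already recorded by category, and should be settled before unblinding. Item 5 is a text change once the intended timing is confirmed. No change to the questionnaire is proposed: section 2.1 dates the trial December 2024 to December 2026, and rewording an item midway could leave answers from two different instruments.

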### Quality control and data management

2.10

Outcome assessors will collect all participant data using paper-based CRFs and subsequently enter the data into an electronic database. The research team will conduct periodic data monitoring to verify completeness, accuracy, and authenticity while concurrently tracking trial progress and adherence to the intervention protocol. To enhance adherence, researchers will maintain regular contact with the participants via telephone or WeChat, providing reminders to actively engage in treatment, scheduled assessments, and follow-up visits. All adverse events and reasons for participant discontinuation—whether from the trial or from follow-up—will be systematically documented.

Acupuncturists, outcome assessors, and statisticians will all receive standardized training on the study protocol to ensure a full understanding of the study procedures and details. Specifically, acupuncturists will complete comprehensive professional training covering acupoint selection and localization, acupuncture techniques, treatment frequency and duration, and distinct protocols for both verum and sham acupuncture, thereby ensuring intervention consistency and fidelity across all participants. All members of the research team will attend scheduled organizational meetings every three weeks to review the progress, identify challenges, and collaboratively resolve issues arising during the trial.

### Sample size calculation

2.11

This trial is an exploratory study. Based on the relevant literature (28, 29) and our preliminary pilot trial, it was predicted that the mean reduction in MAS scores for the acupuncture, sham acupuncture, and basic treatment groups at the end of the intervention would be 2.58, 1.00, and 2.19, with standard deviations of 1.36, 1.62, and 1.48, respectively. The trial employs a 1:1:1 parallel design, with *α* = 0.05 and 1−*β* = 0.9. Considerations for the feasibility of performing this trial and the calculated sample size required per group are 48 cases using the PASS 15.0 software. Accounting for a potential dropout rate of 20%, each group will require 60 participants, resulting in a total sample size of 180 cases.

### Statistical analyses

2.12

All statistical analyses will be performed using IBM SPSS Statistics 25.0. Intention-to-treat (ITT) analysis will be applied to all randomized participants, with missing data handled through multiple imputation methods. Normality tests will be conducted on all data, and continuous variables with a normal distribution will be presented as the mean±SD. Otherwise, the data will be expressed as M (P25-P75). For comparisons among the three groups, continuous variables will be analyzed using parametric tests (ANOVA) or non-parametric tests (Kruskal-Wallis) based on the data features. Categorical variables will be compared using the chi-square test. A *p* value of <0.05 will be defined as statistically significant. Efficacy analyses will be performed on both intention-to-treat (ITT) and per-protocol (PP) populations, with the ITT set including all randomized participants analyzed according to their allocated groups, regardless of protocol deviations, whereas the PP set will consist of participants who comply with the trial procedures without major deviations.

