### Randomization, allocation concealment, and blinding

2.5

Eligible trial participants will be randomly assigned to one of three groups—acupuncture, sham acupuncture, or conventional treatment—using block randomization implemented in the Statistical Package for Social Sciences (SPSS, IBM Corp., NY, USA), version 27. Stratification will be performed according to sex, age, disease duration, and stroke subtype. Randomization codes will be generated by an independent research assistant, placed in sequentially numbered, opaque, sealed envelopes, and distributed to participants only after the completion of baseline assessments.

Participants, outcome assessors, and statisticians will remain blinded to the group allocation throughout the trial. Given the nature of acupuncture intervention, acupuncturists could not be blinded. Blinding codes were securely maintained by an independent researcher who was not involved in participant recruitment, treatment delivery, or outcome assessment. To preserve blinding integrity, participants will be assessed and treated in individual quiet rooms equipped with partition curtains to prevent communication among participants.

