#### Primary outcome

2.7.1

In this trial, the primary outcome will be defined as the change in Modified Ashworth Scale (MAS) scores from baseline to week 4 of treatment. The MAS is a validated clinical tool used to assess the severity of muscle spasticity and evaluate treatment efficacy (19, 20). It comprises six ordinal grades—0, I, I+, II, III, and IV—which correspond to numerical scores of 0, 1, 2, 3, 4, and 5, respectively. Higher grades and scores indicate greater spasticity severity. In this study, MAS assessments will be conducted bilaterally on the biceps brachii and tibialis anterior muscles of patients with PSS.

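### The primary MAS comparison is an unadjusted ANOVA or Kruskal-Wallis test chosen from the data, without baseline MAS or the stratification factors; this gives up precision and may leave no effect estimate

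*Protocol article*

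**What the plan says.** Section 2.7.1 defines the primary outcome as "the change in Modified Ashworth Scale (MAS) scores from baseline to week 4 of treatment". The scale has six ordered grades scored in whole steps from 0 to 5. It is assessed on both sides at two muscles, biceps brachii and tibialis anterior; how the sites are combined is not stated.

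Section 2.5 on randomization states: "Stratification will be performed according to sex, age, disease duration, and stroke subtype".

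Section 2.12 states: "Normality tests will be conducted on all data". Continuous variables found to be normal are shown as mean and SD, other data as median and quartiles. For the three-group comparison, "continuous variables will be analyzed using parametric tests (ANOVA) or non-parametric tests (Kruskal-Wallis) based on the data features". The analysis is by intention to treat, "with missing data handled through multiple imputation methods". The section names no covariate, no between-group difference and no confidence interval; the only criterion is p<0.05.

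**The concern.** Three features of the stated analysis work against the primary outcome.

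- **Baseline.** A change score subtracts baseline but does not adjust for it. Entry requires MAS grades 1 to 3 (section 2.2.1), which are scores 1 to 4 on the coding in 2.7.1. On a single-score reading, a patient entering at 1 can fall by at most 1 and a patient entering at 4 by 4. Change therefore depends on baseline, and that variation stays in the error term.
- **Stratification factors.** Balancing on sex, age, disease duration and stroke subtype and then omitting them leaves standard errors too large wherever those factors are prognostic.
- **Choice of test.** The data decide between a comparison of means and a rank test. Section 2.11 sizes the trial on means and SDs. Kruskal-Wallis does not compare means and gives no difference with a confidence interval. An exploratory trial meant to inform larger ones (section 3.3) needs exactly that estimate.

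**Working it through.** **Inputs.** From section 2.11: mean reductions 2.58 (acupuncture), 1.00 (sham) and 2.19 (basic), with SDs 1.36, 1.62 and 1.48; 48 per group before dropout. The pooled SD of change is √[(1.36² + 1.62² + 1.48²)/3] = √2.221 = 1.49. The correlation r between baseline and week-4 MAS is not given, so a range is assumed.

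**The plan's own figures.** The dropout step reproduces: 48/(1 − 0.20) = 60. The 48 does not: one-way ANOVA on the stated means and the pooled SD needs 22 per group. That is a separate matter and nothing below depends on it.

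**Gain from baseline adjustment, equal variances.** If baseline and week-4 SDs are both s, the change score has variance 2s²(1 − r). ANCOVA leaves s²(1 − r²). The ratio is (1 + r)/2.

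| r (assumed) | Variance ratio | Baseline SD implied, 1.49/√[2(1 − r)] |
|---|---|---|
| 0.3 | 0.65 | 1.26 |
| 0.5 | 0.75 | 1.49 |
| 0.7 | 0.85 | 1.92 |

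Simulation with normal data gave ratios of 0.65, 0.75 and 0.87.

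**Is equal variance possible here?** On a single score with entry values 1 to 4, the largest possible baseline SD is 1.5, with half the patients at 1 and half at 4. So r = 0.7 is impossible under equal variances, and r = 0.5 needs that extreme split.

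**Gain without equal variances.** Keep the change SD at 1.49 and assume a baseline SD s₀ of 0.8 to 1.12 (uniform over 1 to 4: variance (16 − 1)/12 = 1.25). The week-4 SD that fits is s₁ = r·s₀ + √(r²s₀² − s₀² + 2.221), and the ratio is s₁²(1 − r²)/2.221.

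| r (assumed) | s₀ (assumed) | s₁ | Variance ratio |
|---|---|---|---|
| 0.3 | 0.8 | 1.52 | 0.95 |
| 0.3 | 1.12 | 1.38 | 0.78 |
| 0.5 | 0.8 | 1.72 | 1.00 |
| 0.5 | 1.12 | 1.69 | 0.97 |

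**What this means for acupuncture versus basic treatment.** The planned difference is 2.58 − 2.19 = 0.39, with SD √[(1.36² + 1.48²)/2] = 1.42. With 48 per group and two-sided α of 0.05, power is Φ(0.39/[1.42·√(ratio)·√(2/48)] − 1.96). This is 27% unadjusted, 38% at a ratio of 0.65, 31% at 0.85 and 33% at 0.78. Adjustment helps but does not rescue this contrast.

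**Which test would be chosen?** Changes were drawn from normal distributions at the planned means and SDs, rounded to the step of the score, 48 per arm, 3,000 runs. The table shows how often Shapiro-Wilk rejects at 0.05.

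| Score | At least one arm | Pooled raw data | Pooled residuals |
|---|---|---|---|
| Integer steps (one site or a sum) | 99% | 100% | 56% |
| Average of four sites (steps of 0.25) | 18% | 16% | 6% |

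**Type I error of the two-stage choice.** With equal arms, the any-arm rule and the tests named in 2.12, simulated rejection was about 5%.

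**Stratification factors.** The document gives nothing from which to compute their contribution.

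**The case against.** The best defence is that a journal article may leave covariates, estimates and pooling rules to a fuller document, and that this trial calls itself exploratory. That would excuse silence. It does not excuse the comparison that 2.12 actually names, which has no covariates and leaves the test to be chosen from the data.

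Other objections stand and limit the point. A reader might infer each of the following, and the document does not support them:

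- **That the plan defaults to a rank test.** Section 2.12 ties normality testing expressly to presentation and leaves the choice of test to unspecified features of the data. The rank test is a conditional route, and its likelihood runs from near certain to small depending on how sites are combined and what is tested.
- **That adjustment is worth 18% to 54% more patients** (1/0.85 = 1.18; 1/0.65 = 1.54). This needs equal variances, which fit poorly with a single entry score of 1 to 4. A summed score would relax that limit, but the article does not say that the sites are summed.
- **That baseline is ignored.** It is subtracted; regression adjustment is what is missing.
- **That multiple imputation would yield no pooled result.** Kruskal-Wallis chi-square statistics can be combined across imputed data sets by the D2 rule. Only a pooled effect estimate is lacking.
- **That choosing the test from the data inflates false positives.** The simulations do not show this.

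Linear ANCOVA is also not the only defensible model for a six-level score; an ordinal model would serve.

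**Conclusion.** The point holds as one of precision and interpretability. As written, the primary analysis is unadjusted, its form is left to the data, and the factors that shape randomization are absent from it. If the rank route is taken, the trial reports a global p value on its primary outcome and no treatment effect.

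The direction of the precision gain is clear; its size is not. The gain could be about a third of the variance or close to nil, depending on the correlation, the spread of entry scores and the scoring of MAS, none of which the article gives. Any further gain from the stratification factors is unknown. The case for change rests less on a particular percentage than on the facts that the covariates are already collected and that one fixed model removes the uncertainty about which test, and which estimate, will be reported. This is a change that should be made, not an error that invalidates the trial.

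**What to change.** In section 2.12, replace the data-driven choice for the primary outcome with one prespecified model:

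- Outcome: week-4 MAS. Terms: group, baseline MAS scored in the same way as the outcome, sex, age, disease duration and stroke subtype.
- Fit it in each imputed data set, pool the pairwise group differences by Rubin's rules, and report them with 95% confidence intervals.
- State that no normality test selects the primary analysis.
- Keep a proportional-odds or rank analysis as sensitivity.

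Section 2.7.1 also needs a sentence saying how the muscle sites form the MAS score, because the baseline covariate and the outcome both depend on it.

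The cost is wording in these two sections. All covariates are already collected, and no visit, measurement or sample size changes.

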## Abstract

**Background:**

Post-stroke spasticity (PSS) is a common motor complication during stroke recovery, imposing a substantial burden on both individuals and society owing to its high morbidity and disability rates. Current evidence suggests that acupuncture may be an effective intervention for alleviating PSS; however, the efficacy and safety remain uncertain owing to methodological limitations and the generally low quality of the existing evidence. Therefore, this study aims to evaluate the efficacy, feasibility, and safety of acupuncture for PSS and to explore the underlying anti-spasticity mechanisms.

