Research indicates that acupuncture ameliorates motor dysfunction by activating the primary motor cortex (M1) of the ipsilesional hemisphere and promoting brain network remodeling in motor-related areas (12). Acupuncture is currently used to treat PSS. Clinical evidence suggests that acupuncture can alleviate spasticity, enhance motor function, and accelerate rehabilitation and has received a Grade B recommendation for PSS management (13). Experimental studies indicate that acupuncture ameliorates PSS through multiple mechanisms. It modulates the Glu/GABA–glutamine (Gln) cycle via glutamate transporter 1 (GLT-1), thereby rebalancing Glu/GABA levels and mitigating spinal hyperreflexia (14). In addition, it enhances cerebral blood flow in the ischemic penumbra and restores spinal inhibitory control via 5-hydroxytryptamine receptor 2A (5-HT_2A_R)-dependent potassium–chloride cotransporter 2 (KCC2) reactivation, thereby improving limb spasticity (15). However, the majority of the studies are of low methodological quality and lack standardized acupuncture protocols and rigorous study designs. In addition, the potential placebo effects remain incompletely characterized, which may hinder definitive conclusions. Further high-quality research is essential to validate the efficacy and safety of acupuncture for PSS and to elucidate the underlying neuromuscular mechanisms, providing more reliable, evidence-based guidance for personalized prophylaxis and therapy for PSS.

As a solution, we designed a pilot randomized controlled trial (RCT) to assess the preliminary efficacy, feasibility, and safety of acupuncture for PSS and explore the underlying anti-spasticity mechanism of acupuncture.

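### The only group comparison stated for the primary outcome is a three-group omnibus test, which does not by itself address the efficacy of acupuncture; the pairwise contrasts that carry the conclusion should be named

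*Protocol article*

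**What the plan says.** The abstract gives the aim as an assessment of one treatment: "this study aims to evaluate the efficacy, feasibility, and safety of acupuncture for PSS". The Introduction words it more cautiously, as a pilot trial "to assess the preliminary efficacy, feasibility, and safety of acupuncture for PSS". Section 2.7.1 fixes one primary outcome: "the primary outcome will be defined as the change in Modified Ashworth Scale (MAS) scores from baseline to week 4 of treatment".

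The analysis is in section 2.12: "For comparisons among the three groups, continuous variables will be analyzed using parametric tests (ANOVA) or non-parametric tests (Kruskal-Wallis"), the choice between the two depending on the data. For categorical data: "Categorical variables will be compared using the chi-square test". The decision rule is: "A *p* value of <0.05 will be defined as statistically significant".

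Section 2.11 gives expected mean MAS reductions of 2.58 (acupuncture), 1.00 (sham) and 2.19 (basic treatment), SDs of 1.36, 1.62 and 1.48, alpha 0.05, power 0.9, 48 per group, and 60 per group after 20% dropout. It ties these to no contrast. Section 3.1 explains why the sham needles and the basic treatment group are there, but attaches no hypothesis to either comparator and does not rank them.

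**The concern.** The aim concerns one arm and has a direction: does acupuncture do better than sham, and better than basic treatment? The stated test asks something else, namely whether all three means are equal. It rejects for any departure, including a gap between sham and basic treatment that says nothing about acupuncture.

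The planning values make this more than a textbook remark, because they place sham 1.19 points below basic treatment. A gap of that size is enough on its own to make the omnibus test significant in nearly every trial. If the report rested on the omnibus p-value, it could be read as evidence for acupuncture when there is none against the comparator that matters. Unless the contrasts are fixed in advance somewhere, the emphasis between the two comparators also stays open.

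**Working it through.** **Inputs (section 2.11).** Means A = 2.58, S = 1.00, B = 2.19 (acupuncture, sham, basic). SDs 1.36, 1.62, 1.48. n = 48 per group evaluable, or 60 with no dropout. Alpha 0.05, taken as two-sided for pairwise tests (an assumption; sidedness is not stated).

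**The plan's own figures.** The dropout step reproduces: 48/0.8 = 60. The 48 does not come from an omnibus ANOVA with these inputs, which needs 22 per group for 90% power (19 to 26 for a common SD from 1.36 to 1.62). That is a separate matter, and nothing below depends on it.

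**Omnibus power.** The common variance is (1.36² + 1.62² + 1.48²)/3 = 6.6644/3 = 2.2215 (SD 1.490). The noncentrality is λ = n·Σ(μᵢ − μ̄)²/2.2215, and power is the upper tail of the noncentral F with 2 and 3n − 3 degrees of freedom.

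| Scenario (A/S/B) | Σ(μᵢ − μ̄)² | λ at 48 | Power at 48 | Power at 60 |
|---|---|---|---|---|
| Planning values 2.58/1.00/2.19 | 1.355 | 29.3 | 99.9% | >99.9% |
| Acupuncture = basic 2.19/1.00/2.19 | 0.944 | 20.4 | 98.5% | 99.7% |
| Acupuncture = sham 1.00/1.00/2.19 | 0.944 | 20.4 | 98.5% | 99.7% |

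Simulation with the three unequal SDs and normal data at 48 per group gives about 98% when acupuncture equals basic treatment and about 99% when it equals sham. Kruskal-Wallis gives about 98% in both. At the planning values the sham mean alone supplies (1.00 − 1.923)² = 0.852 of the 1.355, or 63% of the between-group sum of squares.

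**Pairwise power at the planning values (two-sided 0.05).** SE = √((s₁² + s₂²)/n).

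- Acupuncture versus sham: difference 1.58; SE = √((1.8496 + 2.6244)/48) = 0.305; ratio 5.18; power above 99%. For 90% power, 20 per group suffice.
- Acupuncture versus basic treatment: difference 0.39; SE = √((1.8496 + 2.1904)/48) = 0.290; ratio 1.34; power about 26–27%. At 60 per group, SE = 0.259, ratio 1.50, power about 32%. For 90% power, 281 per group would be needed.

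**How named contrasts behave in the two equality scenarios (48 per group).**

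- Acupuncture = sham: acupuncture versus sham is significant in about 5% of trials, the nominal rate, against about 99% for the omnibus test.
- Acupuncture = basic: acupuncture versus sham is still significant in about 97% of trials, correctly, because the means differ by 1.19. Acupuncture versus basic treatment is significant in about 5%. Here only the second contrast shows that nothing is gained over basic treatment.

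**The case against.** Four points deserve weight.

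1. Section 2.12 is one paragraph of a condensed article. It does not say that the omnibus p-value is the sole basis for the conclusion or that no pairwise tests follow; those may be set out in a full protocol or SAP that is not shown. This stands, so the absence of post-hoc detail is not the point. What remains is that the one test stated for the primary outcome does not match the stated aim. Which contrast answers the question is also a protocol-level choice, since the sample size and the conclusion both depend on it.
2. With exactly three groups, an omnibus test followed by unadjusted pairwise tests controls the familywise error under equal variances. This also stands: an omnibus gate is a legitimate first step. It still leaves the conclusion to contrasts that the article does not name.
3. At the planning values the omnibus test hardly ever misleads about sham. It is significant without acupuncture beating sham in roughly 0.04% of trials. The mismatch appears when the acupuncture effect is not as predicted, which is what the trial is meant to find out.
4. The trial calls itself a pilot and exploratory, and its limitations section leaves definite efficacy to later multi-centre trials. This lowers the severity.

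A reader might infer that the trial cannot answer whether acupuncture works. The documents do not support that: pairwise contrasts can be computed from the same data, and acupuncture versus sham has ample power at the planning values. A reader might also take the large share of simulated trials in which the omnibus test is significant while acupuncture versus basic treatment is not as proof of a wrong test. That share mostly restates the low power of the second contrast, which is a sample-size matter.

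**Conclusion.** The point holds in limited form: a significant omnibus result does not by itself show that acupuncture is better than either comparator. At 48 per group it would be expected in about 98% of trials with acupuncture equal to basic treatment, and about 99% with acupuncture equal to sham.

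These figures assume normal data, the planning SDs and the predicted 1.19 gap between sham and basic treatment. With two equal means and a smaller gap to the third, omnibus power at 48 per group falls: 93% for a gap of 1.0, 77% for 0.8, 51% for 0.6. The logical mismatch remains at any gap, but its practical size depends on this one.

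Naming acupuncture versus sham does not settle everything either, since beating sham alone does not show a benefit over basic treatment. The change should be made, but the pilot and exploratory status does not justify calling it indispensable.

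**What to change.** In section 2.12:

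- State that the efficacy conclusion rests on named pairwise contrasts in MAS change from baseline to week 4, each with an estimate and 95% CI.
- Make acupuncture versus sham the primary contrast at two-sided 0.05, and test acupuncture versus basic treatment only if the first is significant. Another pre-stated order, or an alpha adjustment, would also serve; what matters is that the rule is fixed beforehand.
- Treat the omnibus test and sham versus basic treatment as supportive.
- State that acupuncture versus basic treatment has about 26–27% power at 48 per group (about 32% at 60) at the planning values, so a non-significant result there is inconclusive, and that success against sham alone does not show benefit over basic treatment.

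The cost is a few sentences, with no change to data collection. The downside of the fixed sequence is that acupuncture versus basic treatment can be claimed only after acupuncture versus sham succeeds. Rewording does not cure the low power of the second contrast, which would need far more patients.
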